#### Data management

All data in the study will be collected electronically and will be held securely on password-protected computers that can be accessed only by the members of the research group. To protect participant confidentiality, unique anonymous study IDs will be used for data storing, tracking, and reporting. The data cleaning process will actively search for errors in a planned way. Multiple imputation will be used to handle missing data as its validity in handling missing data in RCT and is available for most types of data [66].

### Data analyses

#### Quantitative data

The intention to treat principle will be used to analyze the intervention preliminary effectiveness with primary and secondary outcomes, which include all participants randomized to a treatment arm regardless of treatment adherence, attrition, or the completion of outcome assessments. The preliminary analysis will be conducted to examine the distribution of variables for skewness, variability, missing data, and outliers, following previous internet-based intervention on depression [15]. Participants’ sociodemographic information and depression severity will be compared between groups using statistical analyses depending on the variable.

The descriptive statistical analyses (i.e., central tendency and dispersion tendency) and graphical methods will be used to summarize baseline characteristics of all key variables. For example, mean, standard deviation, and range of the total number of participant’s log-in activities will be calculated to represent participants’ engagement in the SbS-F program. The quantitative data from implementation measurements (i.e., stakeholders’ attitude toward evidence-based practice) will also be analyzed with descriptive statistical analyses. Comparison of primary and secondary outcomes between groups (control vs intervention) from baseline to follow-up measurements will be performed using a general linear mixed model with adjustment for possible confounders (i.e., and time effect). In particular, the following sociodemographic variables will be controlled as previous studies [7, 59] showed its association with depressive and anxiety symptoms among Filipino communities: sex, marital status, educational level, income level, and language proficiency. The difference of outcomes between the two groups will be covered within the 95% confidence interval for the effect size. The effect sizes (Cohen’s *d*) will be calculated by dividing the estimated mean difference (from baseline, monitoring, endline, to follow-up) reported from the linear mixed model results by the pooled standard deviation (*SD*) at baseline. The effect size will be calculated to inform the power calculations for the planned definitive trial.

The size and pattern of missing data and the reasons will also be documented. Missing data will be analyzed that will investigate the associations between (1) observed variables and patterns of missingness, (2) treatment conditions on rates of missingness and time to missingness; and (3) baseline characteristics and missingness [45]. The sensitivity analyses of treatment completers (participants who finished at least three of five SbS-F modules) will also be measured with the general linear mixed models. The relative risk (RR) and 95% confidence intervals (CIs) for the number of patients who recover from depressive disorder in the SbS-F compared with the ECAU group will be reported in the sensitivity analyses. All the quantitative analyses were performed using SAS Statistical Package 9.4 (SAS Institute Inc., Cary, NC).

#### Qualitative data

All individual interviews and focus group discussions records will be transcribed. The qualitative data then will be analyzed with deductive thematic analysis framework based on the RE-AIM domains assessed, which will be used to develop an initial codebook. The data will be coded separately by stakeholder group (e.g., participants, e-helpers, and community partner staff). An iterative approach will be used in analyzing the qualitative data where two coders will double-code all transcripts and discuss the discrepancies until consensus is reached. A master codebook will be entered into a qualitative analysis software.

## Discussion

Over 30% of OFWs in Macao reported depression and anxiety and more than 25% for PTSD [8–11], which are more than two times higher than in the local Macao Chinese population [12]. However, mental health services in Macao for OFWs are very limited and more expensive compared with services for local people. A digital mental health intervention may be useful in addressing OFWs’ psychological distress. Therefore, this study aims to evaluate the effectiveness of the SbS-F mobile application intervention, compared to ECAU, and to evaluate the SbS-F’s potential for implementation in real-world settings through collaboration with local community partner.

To our knowledge, this is the first intervention trial of online mental health intervention ever conducted in Macao, or among OFWs. The hybrid type 1 effectiveness-implementation randomized controlled trial is chosen to accelerate the translation of clinical research into more effective implementation strategies and policies, especially within the rapid development of technology and information system [29]. Specifically, RE-AIM framework and embedded mixed methods are used to support this hybrid effectiveness-implementation trial in decreasing the discrepancies from trial findings to sustainability of evidence-based practices [30–32].

However, this pilot trial may face two main challenges. First, there is potential for high attrition as reported in previous online mental health intervention trials [15, 67, 68]. To anticipate this issue, all possible recruitment channels have been identified and attrition rate has been included in sample size calculations. Second, it is not possible to blind the participants in this study. Nevertheless, participants will be informed about the importance of two-arm study design and will be encouraged not to tell their peers about what group of treatment they are allocated.

## Conclusion

In summary, this study will provide important new knowledge about the preliminary effectiveness of SbS-F, a mobile application, as a digital mental health intervention and its scalability. If SbS-F shows a significant positive effect toward primary (depression) and secondary (anxiety and wellbeing) outcomes among OFWs in Macao, it has strong potential to be used by OFWs in other countries that may also experience depression and difficulty accessing mental health services. Simultaneously, this pilot hybrid type 1 study will also evaluate the possibility of SbS-F implementation and scale-up in real-world setting through collaborative work with a local community partner.

## Data Availability

The data that support the findings of this study are available from the corresponding author upon reasonable request.

## Appendix 1

**Table 4 Tab4:** Study timeline

Step	Month											
	1	2	3	4	5	6	7	8	9	10	11	12
Preparatory works for SbS-F mobile application	**x**	**x**	**x**	**x**								
Recruiting and training e-helpers			**x**	**x**	**x**	**x**						
Internal SbS-F testing and e-helpers simulation					**x**	**x**						
Participants recruitment, screening, and randomization							**x**	**x**	**x**			
Intervention								**x**	**x**	**x**		
Follow-up and implementation evaluation									**x**	**x**		
Quantitative data cleaning and analysis										**x**	**x**	
Qualitative data analysis										**x**	**x**	
Data integration											**x**	**x**
Dissemination							**x**	**x**	**x**	**x**	**x**	**x**

## Appendix 2

**Table 5 Tab5:** Overview of intervention

Content	Content overview

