**Fig. 2 Fig2:**
[figure not shown]
Overview of SbS-F hybrid trial study design following CONSORT diagram

**Table 1 Tab1:** The Reach, Efficacy/Effectiveness, Adoption, Implementation, and Maintenance (RE-AIM) framework

Domain and outcome (example)	Source
**R**each • Participant’s and decliner’s characteristics (e.g., compare sociodemographic information between participant and nonparticipant OFWs; reasons for not participating; the most effective recruitment strategy)	• Administrative data • Open-ended questions in a questionnaire
**E**ffectiveness • Primary outcome (depression severity) • Secondary outcome (anxiety and wellbeing) • Reason for withdrawing	• Questionnaires • Interviews and focus groups
**A**doption • Ineligibility reasons • Barriers and enablers of SbS-F adoption into community partner’s program and recommendations for addressing barriers and maximizing adoption • Community partner’s knowledge and beliefs about the SbS-F program	• Administrative data • Questionnaires • Interviews and focus groups
**I**mplementation • Participants’ adherence to the intervention (e.g., duration in accessing the SbS-F and reasons for missing sessions) • Participants’ perceived benefit from the intervention • Barriers and enablers in implementing the program and modifications needed to maximize the implementation (from participants’ and staff’s perspective) • Relevance of the SbS-F story and techniques in participant’s lives • Time and resources required for supporting the program (e.g., number of e-helpers needed and their total working time; e-helpers’ training, selection, and retention)	• Administrative data • Questionnaires • Interviews and focus groups
**M**aintenance • Attrition rates • The durability of intervention effects on depression • Resources, strategy, and policy needed to integrate and maximize the SbS-F intervention into community partner’s program after the study ended	• Administrative data • Questionnaires • Interviews and focus groups

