### Setting and timeline

This pilot trial will take place in Macao among OFWs over 12 months (Appendix 1). The total population of OFWs in Macao as of March 2020 is 34,034 (women 65.3%) [35]. Most of OFWs (50.5%) are working in domestic work, followed by hospitality (18.1%), real estate, renting, and business activities (14.9%), and recreation and gaming (6.9%) industries [36]. A population survey among female Filipino domestic workers in Macao [19] found that their median income was MOP 3700 (∼ USD 460; (*IQR* = 3500–4000) per month and the median time working as an OFW was 6 years (*IQR* = 2–11). The median of working time was 67.8 h per week (*IQR* = 52–78) with 4 days off per month. Most participants owned a smartphone (91.3%) and could access internet from their smartphone (77.9%). Additionally, more than 75% of participants can access Wi-Fi to reduce the use of their own data plan. Only 12.6% of participants reported no intention to access professional mental health services.

However, to the authors’ knowledge, there is no official record on migrant workers’ use of health services, including mental health services, and a lack of clear information regarding migrant workers’ health insurance and its coverage for mental health services. In addition, progress in available mental health services of Chinese mental health care system is still only found on government structural level and applied in few big cities in the mainland China for its citizens [37]. As a result, migrant workers (including OFWs) in Macao may face challenges to treat mental disorders that arise during their work period. For example, there is only one public hospital available and the psychology/psychiatry department is only open from Monday to Friday, during times that migrant workers usually work. Alternatively, migrant workers can access a private hospital for mental health services in the weekend. But the fee in the private hospital is 10 times higher than public hospital and this fee roughly equals with 1/6 of their monthly income for one session of psychotherapy.

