### Intervention

#### Intervention and control groups

The digital mental health intervention in this study is a mobile and web application named Step-by-Step for Filipino users (SbS-F). The original SbS program was developed by experts in the field of psychology, psychiatry, and global mental health in concert with colleagues at the WHO [20]. Behavioral activation (BA) is the primary treatment component in the intervention, which is simple and effective at reducing depressive symptoms [39, 40] and can be delivered digitally with minimum assistance [41]. Previous trials (e.g., [15, 42]) demonstrated that BA could be delivered by lay health workers, in person and digitally, to reduce anxiety, depression, and PTSD. Also, BA for PTSD among American veterans was associated with greater reduction in depressive symptoms and higher treatment satisfaction than treatment as usual [43].

The SbS-F program content is delivered through a series of illustrated sessions that teach users specific skills that can be applied to reduce psychological distress (Appendix 2). The sessions articulate into an overall story which is delivered by two main characters, available in female and male versions. They guide the user through the intervention content in an interactive, supportive, and culturally appropriate manner. As informed by our cultural adaptation, the first main character is a wise community elder and the second character is a younger person who applied the Step-by-Step techniques themselves.

Each character teaches the user about the program, the intervention techniques and why they work, and model how to apply them through easy to follow real-world examples. The community elder character also teaches the user techniques in greater detail and coaches on how to complete intervention activities. This type of illustrated and adapted format is shown to be an effective digital mental health intervention format [44]. The five therapeutic sessions are summarized in Table 2 below. The intervention will be available online (in mobile application format) with “contact-on-demand” support from trained research assistants called e-helpers. For participants in the intervention group, e-helpers will contact them to explain briefly the SbS-F application.

**Table 2 Tab2:** Key intervention information

Week	Control group	Intervention group
1	Baseline assessment	Baseline assessment
2	Brief psychoeducation and referral	Onboarding (introduction to the SbS-F mobile application)

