3		Session 1: Get started (psychoeducation and trying small and pleasant activities)
4		Session 2: Get active (behavioral activation)
5		Session 3: Beat obstacles (more complex behavioral activation and relaxation)
6		Session 4: Get together (increasing social support)
7		Session 5: Keep it up (relapse prevention).
8	Endline assessment	Endline assessment
20	Follow-up assessment	Follow-up assessment

*Note*. *SbS-F* Step-by-Step program (Filipino version)

On the other side, participants in control group will receive ECAU, which consists of brief psychoeducation on depression and a referral to CM services. This basic depression psychoeducation is formulated based on the information provided during the first session of SbS to assure that the information is same between two groups. A previous study found that online psychoeducation reduced depressive symptoms among adults in Indonesia [15]. In addition, participants will receive information on services provided by CM. There are two CM departments named WelAnser Centre (WC) and Life Hope Hotline (HH) that can be accessed by participants. In WC, there are three social workers with Bachelor of Social Work degree who handle mental health problems of migrant workers with supportive counselling services. These social workers received mental health-related education in their bachelor’s degree and practical mental health care trainings through the Macao Social Welfare Bureau. If the issue is beyond the social worker’s expertise or CM’s scope of service, the client will be referred to another agency. For example, a client who needs medication will be referred to the hospital and accompanied by the social worker as needed.

Due to geographical and time difficulties, not all OFWs can visit the WC to have counselling. Alternatively, they can contact HH for emotional support through phone counselling that is available 24/7. The phone counselling provided by HH is available in Cantonese, Mandarin, and English, with counsellors from a social work or psychology bachelor’s degree background. Moreover, every counsellor at HH has been trained about mental health and crisis intervention. In addition, there is a regular supervisory meeting to discuss any challenges faced by the counsellors. Similar with the counsellors at WC, if the client’s problem is beyond their expertise or CM’s available services, the counsellor will provide client information about other agencies that may be able to assist their needs.

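### The calendar in Table 4 and the 12-month study length cannot accommodate the week-20 follow-up set in Tables 2 and 3

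*Protocol article*

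**What the plan says.** **Visit schedule.** Table 2 (Intervention and control groups) and Table 3 (Assessments) agree: baseline at week 1, sessions 1 to 5 in weeks 3 to 7, endline at week 8, and "Follow-up assessment" at week 20, in both arms. Table 3 collects the PHQ-9, GAD-7 and WHO-5 at week 20.

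**Calendar.** Appendix 1, Table 4 has twelve monthly columns:

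- "Participants recruitment, screening, and randomization": months 7, 8 and 9
- Intervention: months 8, 9 and 10
- "Follow-up and implementation evaluation": months 9 and 10
- "Quantitative data cleaning and analysis": months 10 and 11

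The section Setting and timeline gives the whole trial 12 months and points to this appendix.

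**Use of the week-20 data.** Table 1 lists "The durability of intervention effects on depression" under Maintenance. The Quantitative data section plans "Comparison of primary and secondary outcomes between groups (control vs intervention) from baseline to follow-up measurements" with a linear mixed model.

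**The concern.** The follow-up row ends in the same month as the intervention row. Yet Table 2 puts 13 weeks between session 5 (week 7) and follow-up (week 20). The two schedules therefore cannot both be followed.

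The week-20 visit matters to the plan. Participants are compensated for it, eligibility requires an intention to stay in Macao for at least 6 more months, and it is the latest outcome measurement in Table 3. If the team works to Table 4, week-20 data would be missing for administrative reasons that depend on enrolment date, over and above the 50% drop-out that the protocol already expects. The durability question would then be answered from early enrollees only, or not at all.

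**Working it through.** **Inputs.** Recruitment months 7–9, follow-up row to the end of month 10, analysis row to the end of month 11, study end at month 12 (Table 4; Setting and timeline). Baseline week 1, endline week 8, follow-up week 20 (Tables 2 and 3).

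**Set-up.** Day 0 is the first day of month 7, taken as the earliest possible baseline. Let m be the month length in days: 30.44 on average, with 28 and 31 as outer bounds. The lag L to follow-up is 19 × 7 = 133 days to the start of week 20, or 20 × 7 = 140 days to its end.

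**Step 1: can the first enrollee be followed up by the end of month 10?** The time available is 4m days.

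| m (days) | Available (4m) | In weeks | Shortfall, L = 133 | Shortfall, L = 140 |
|---|---|---|---|---|
| 28 | 112 | 16.0 | 21 days | 28 days |
| 30.44 | 121.75 | 17.4 | 11 days | 18 days |
| 31 | 124 | 17.7 | 9 days | 16 days |

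The shortfall is positive in every case. The share reaching week 20 inside the follow-up row is 0%, whatever the enrolment pattern.

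**Step 2: when do the week-20 visits fall?** With average months, L is 133/30.44 = 4.37 to 140/30.44 = 4.60 months.

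- First enrollee: 6.0 + 4.37 to 6.0 + 4.60 = 10.4 to 10.6 elapsed months, which is in month 11.
- Enrolled at the end of month 9: 9.0 + 4.37 to 9.0 + 4.60 = 13.4 to 13.6 elapsed months. This is in month 14, 1.4 to 1.6 months after the study ends.

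**Step 3: what share reaches week 20 by later dates?** This assumes uniform enrolment over the 3m days of recruitment. The protocol does not state an enrolment pattern. The share by the end of month T is ((T − 6)m − L) / 3m, before any drop-out.

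| m (days) | End of month 11 | End of month 12 |
|---|---|---|
| 28 | 0/84 to 7/84 = 0–8% | 28/84 to 35/84 = 33–42% |
| 30.44 | 12.2/91.3 to 19.2/91.3 = 13–21% | 42.6/91.3 to 49.6/91.3 = 47–54% |
| 31 | 15/93 to 22/93 = 16–24% | 46/93 to 53/93 = 49–57% |

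**Step 4: the week-8 endline.** The lag is 49 to 56 days, or 1.61 to 1.84 average months. The last enrollee reaches it at 9.0 + 1.61 to 9.0 + 1.84 = 10.6 to 10.8 elapsed months. That is in month 11, after the intervention and follow-up rows close but before the analysis row does. Under uniform enrolment, (4 − 1.84)/3 to (4 − 1.61)/3 = 72–80% reach week 8 by the end of month 10.

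**Step 5: a check from the intervention row.** Suppose session 1 (week 3) takes place on the first day of month 8, when that row opens. Week 20 is 17 weeks or 119 days later, which is 3.9 months and falls late in month 11. The follow-up row is missed on this reading too.

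**The case against.** **Table 4 may simply lack a row.** The row opens about 60.9/7 = 8.7 weeks after recruitment begins. That suits the week-8 endline and the implementation measures, so the authors may have omitted a line for week 20 and not meant to cut it short. This is plausible, and it makes the data loss conditional on the team following the calendar. It does not remove the conflict: no row would then provide for week 20, and 12 months would still be too short for later enrollees.

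**The between-arm comparison is largely protected.** Randomisation in permuted blocks of 2, 4 or 6 keeps the arms close to balanced over calendar time, so missingness tied to enrolment date should fall about equally on both. This stands. The loss is mainly of precision and of durability information, in a pilot that calls its effectiveness questions exploratory.

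**Stronger readings that the document does not support:**

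- *Endline would be analysed incomplete.* All week-8 data can arrive by the end of month 11, while the combined cleaning and analysis row is still open. Starting to clean data in month 10 does not mean analysing a partial outcome. The protocol also names no primary time point.
- *The whole Maintenance domain is lost.* Table 1 also lists attrition rates there, and administrative data are among its sources. What is exposed is durability and the instruments that Table 3 places at follow-up.
- *Nobody reaches week 20 within 12 months.* Early enrollees can, but only after the follow-up row has closed and in most cases after the analysis row has closed.

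**Conclusion.** The point holds as an internal contradiction of dates, not as missing detail. Table 4 and the 12-month duration cannot contain the week-20 visit of Tables 2 and 3. That no participant can be followed up by the end of month 10 holds for every month length and both readings of week 20, and needs no enrolment assumption. So does the finding that someone enrolled at the end of month 9 reaches week 20 only in month 14.

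The partial shares do rest on uniform enrolment: about 13–21% by the end of month 11 with average months, and 33–57% by the end of month 12 across month lengths. If the calendar is followed, the week-20 durability data and the final point of the mixed model would be absent or drawn from early enrollees. The endline is not lost, although the intervention and follow-up rows close a month too early for the last participants.

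**What to change.** Reconcile Table 4 and Setting and timeline with Tables 2 and 3, in one of three ways:

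1. **Extend the calendar.** Run the intervention and endline row to month 11 and the follow-up row over about months 11 to 14. Start the week-20 analysis after the last follow-up visit, and state a study length of more than 12 months. The cost is a few more calendar months of online assessment, with no new procedures or participants.
2. **Keep 12 months and bring recruitment forward**, so that the last week-20 visit precedes data lock. As an illustration, a last visit by the end of month 11 needs the last enrolment by 11 − 4.6 = 6.4 elapsed months. A three-month recruitment would then open at about 3.4 elapsed months, in month 4. Table 4 has e-helper training and app testing running to month 6, so preparation would have to be shortened or overlapped.
3. **Split the reporting.** State that only endline is analysed in the 12-month period and that durability is reported later, with a date. This costs wording now, but the week-20 visits still have to be collected after month 12.

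In each case, give the week-20 visit its own row in Table 4, separate from the implementation evaluation.
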